#### Healing caps placement

After 6 months of implant placement, healing caps will be placed to begin the prosthetic phase. The cover screw will be removed, RFA will check the secondary implant stability, and the healing cap installed. In the cases where mini-implants were used, they will be retrieved by trephine drills for posterior analysis [19].

### Criteria for discontinuing or modifying allocated interventions {11b}

Criteria were not applied because the study will evaluate a medical device in a split-mouth allocation; therefore, it is impossible to change the allocation once the device is installed. The patient will be discontinued from the study only if they experience a serious adverse event, which can be correlated with the device. So far, we have foreseen a serious allergic reaction to the device material and a serious infection.

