### Objectives {7}

The primary objective of this clinical investigation is to evaluate the increase/maintenance of bone graft volume after eight months postoperative when a synthetic patient-specific block graft is used compared to an intra-oral autogenous graft. The secondary objectives include the analysis and characterization of the new bone formation according to the graft used; Plenum^®^ Oss 3D_β_ fit, or autogenous; surgical particularities arising from the type of graft, such as the adaptation of the graft in the host bone; and operative time. In addition, implant stability and the adverse effects from both grafts and surgical procedures performed to install each kind of graft will also be analyzed.

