### Provisions for post-trial care {30}

According to the Brazilian law (CNS Resolution No. 466 of 2012, items II.21 and IV.3.g), this trial will assure the participant and the companion of the reimbursement of expenses arising from the participation and the presence for consultations. Additionally, if any damage occurs to the participant due to the interventions from this research, the participant will be compensated and will receive full assistance for the necessary time (CNS Resolution No. 466 of 2012, items II.3.1 and II.3.2).

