### Participant timeline {13}

**Table Tabb:** 

	Study period				
	Enrollment	Allocation	Post allocation		
Timepoint	− ***T***_**1**_	T0	T1 (intervention)	T2 (8-month follow up)	T3 (14-month follow up)
Patients visits	x				
Eligibility screen	x				
Informed consent	x				
Randomization: split-mouth		x			

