**Assessments**					
Surgery analysis			x		
Implant stability				x	x
Biopsies				x	
Biopsies analyses				x	x
Adverse events			x	x	x

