### Sample size {14}

Sample calculations were performed based on tomographic bone formation data from the study, which evaluated the volumetric stability of autogenous and allogeneic corticomedullary block grafts used for volume increase associated with edentulous alveolar ridges [19]. This choice was due to the lack of studies comparing β-tricalcium phosphate blocks and autogenous bone and the similarity of the methodology for evaluating the stability of block grafts. As a result, it was verified that the minimum difference between the means of treatments concerning the percentage of volumetric reduction of the graft was 11.90, with a standard deviation of 12.09. Therefore, considering a study power (1-β) of 0.8 and an *α* power of 0.05, a minimum sample of 20 participants was determined, each of whom will receive two grafts, one synthetic in a personalized block and another in an autogenous block. To maintain the power of the study, the sample size should be maintained, thus if any participant dropout or is discontinued before the analysis of the primary outcome, a new participant will be recruited instead, until complete 20 participants.

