### Plans to promote participant retention and complete follow-up {18b}

Data from participants which have already been collected will be used in the analysis referring to the completed steps, even if they do not conduct the clinical investigation.

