### Interim analyses {21b}

The principal investigator will decide to suspend the study if any serious adverse event is reported until the cause is identified. If it is verified that the event was not related to the medical device, the study will restart under sponsor permission. However, if the cause of the serious adverse event is related to the investigational device and the investigation is terminated, the interim results will be accessed by the principal investigator, that will perform the correspondent analysis.

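### A serious device-related event takes the patient out of the whole study, so the scheduled 8- and 14-month adverse-event assessments may be missed

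*Protocol article*

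**What the plan says.** The Protocol article gives one reason for taking a patient out, under Criteria for discontinuing or modifying allocated interventions {11b}: "The patient will be discontinued from the study only if they experience a serious adverse event, which can be correlated with the device". The same section notes that the allocation cannot be changed once the device is in place. It names a serious allergic reaction to the material and a serious infection as the foreseen triggers.

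Other sections bear on what follows:

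- **Objectives {7}:** "the adverse effects from both grafts and surgical procedures performed to install each kind of graft will also be analyzed".
- **Participant timeline {13}:** the row "Adverse events" is marked at the intervention, at 8 months and at 14 months.
- **Section {18b}, on retention:** "Data from participants which have already been collected will be used in the analysis referring to the completed steps", including for those who do not finish.
- **Sample size {14}:** "if any participant dropout or is discontinued before the analysis of the primary outcome, a new participant will be recruited instead", until 20 are complete.
- **Provisions for post-trial care {30}:** if the interventions cause harm, "the participant will be compensated and will receive full assistance for the necessary time".
- **Adverse event reporting and harms {22}:** adverse effects go into the case report form, with a phone call if serious, and further action follows a named national regulation that is not shown.

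**The concern.** The rule does not separate two different decisions: stopping further study procedures and ending observation. Stopping procedures can be right. A patient with a serious infection at the graft may be unfit for the 8-month biopsy, trial implants and mini-implants. Ending observation is a separate matter, and leaving the study does not by itself end exposure, because the graft is described as resorbing slowly.

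At stake is how complete the adverse-effect description is. Whether a serious infection or allergic reaction resolves, recurs or costs the graft belongs in that description. So do later events at the test, control and donor sites in the same patient. The rule permits scheduled observation to stop in the very patients who had serious device-related harm.

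**Working it through.** The point rests on no figure computed in the protocol, so there is none to reproduce. The check sets the sections side by side and counts assessments. I use months rather than T labels, because the Tomography section and the timeline table number their timepoints differently.

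**Inputs.** From the timeline {13}, adverse-event assessments are scheduled at month 0 (intervention), month 8 and month 14, three in all. From {11b}, a patient with a serious device-related event at month m leaves the study.

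**Formula.** Assessments at risk = number of scheduled months in {0, 8, 14} later than m.

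| Time of event | Still due | At risk |
|---|---|---|
| 0 < m < 8 | months 8 and 14 | 2 of 3 |
| 8 < m < 14 | month 14 | 1 of 3 |

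**Scale.** The protocol gives no event rate, so the number of affected patients is an assumption. One to three such patients before month 8, set against the target of 20, would be 1/20 = 5% to 3/20 = 15%. Between 1 × 2 = 2 and 3 × 2 = 6 scheduled assessments would be at risk. No probability is attached to this range.

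**Does another section restore the follow-up?**

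1. {18b} makes use of data already in hand. It creates no later collection.
2. {14}, and the section on non-adherence and missing data {20c}, replace the patient. This restores the count for the primary endpoint, not the course of the harmed patient's event.
3. {22} registers and reports the event. It says nothing of assessment after discontinuation.
4. {30} provides care and compensation, which is not study data collection.
5. Interim analyses {21b} acts on the whole study. The study is suspended until the cause is known and restarts if the device was not responsible. Access to interim results is foreseen "if the cause of the serious adverse event is related to the investigational device and the investigation is terminated". Termination is there a further condition and does not follow automatically from device causation, so the trial could continue without the affected patient.

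None of the five keeps the individual patient in the scheduled assessments.

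**The case against.** The strongest reply is that {11b} concerns interventions and does not say that safety observation stops. On this view the concern turns silence into a rule, and follow-up after discontinuation is detail that an article leaves to the full protocol or to the cited regulation. {18b} does not bar later safety data. The event is captured, the suspension implies that it will be investigated, and the patient is cared for. The fractions count columns of a condensed table whose intervention column may cover several early contacts. Finally, month 8 is implant surgery and month 14 is healing-cap placement, so a patient whose procedures have stopped has no procedural reason to attend.

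Part of this stands. The text does not say outright that recording ends, clinicians would probably follow such a patient in practice, and the regulation's content cannot be judged here. That is why the claim is only that assessments may be missed. The fractions measure scheduled assessments, not information lost. An adverse-event contact without surgery would also be new in content for these patients.

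The rest does not answer the point. The article does not leave discontinuation open: it states a rule, and the rule removes the patient from the study. Read with the timeline and the objective, it gives a worse result than a rule limited to procedures. An analysis plan cannot recover visits that did not take place. Several early contacts within the intervention column would not change which later assessments are at risk.

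**Conclusion.** The concern holds, as a minor point of design. As worded, the discontinuation rule puts at risk two of three scheduled adverse-event assessments for an event before month 8, and one of three for an event between months 8 and 14.

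This assumes that discontinuation from the study means what it says, and that neither the full protocol nor the cited regulation adds follow-up that cannot be seen here. The number of affected patients is unknown and probably small, and the trial might be suspended or ended after such an event. The direction of any bias is not established, since both sides of the mouth and the donor site leave observation together. The volume analysis is not part of this point.

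**What to change.** Reword {11b} along these lines: after a serious adverse event related to the device, further study procedures (biopsy, trial implants, mini-implants) may be stopped, but the patient remains in adverse-event follow-up until the event resolves and through the 8- and 14-month timepoints, unless consent is withdrawn. Add that such patients are included in the adverse-effect summary even when replaced under {14}.

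The cost is one or two sentences of protocol text, plus a short adverse-event assessment at existing timepoints for the few patients affected. For those whose surgery is cancelled, this means a contact for adverse events alone. No extra participants or procedures are needed.

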### Strategies to improve adherence to interventions {11c}

Adherence will be maximized by educating patients about post-operative care and the importance of this process to the treatment successful.

### Relevant concomitant care permitted or prohibited during the trial {11d}

After the grafting procedure, the postoperative prescription will include Amoxicillin 875 mg + Potassium Clavulanate 125 mg every 12 h for 7 days, Nimesulide 100 mg every 12 h for 3 days, and Dipyrone 500 mg every 6 h for 3 days. Implant post-surgical medication will include Amoxicillin 500 mg every 8 h for 7 days, Nimesulide 100 mg every 12 h for 3 days, Dipyrone 500 mg every 6 h for 3 days, and chlorhexidine digluconate twice a day for 15 days.

Steroids and other drugs that interfere with calcium metabolism should not be administered during this clinical investigation, as described in the exclusion criteria.

### Provisions for post-trial care {30}

According to the Brazilian law (CNS Resolution No. 466 of 2012, items II.21 and IV.3.g), this trial will assure the participant and the companion of the reimbursement of expenses arising from the participation and the presence for consultations. Additionally, if any damage occurs to the participant due to the interventions from this research, the participant will be compensated and will receive full assistance for the necessary time (CNS Resolution No. 466 of 2012, items II.3.1 and II.3.2).

### Outcomes {12}

#### Primary endpoints

Evaluate the gain of increase/maintenance of the volume of the bone graft area and the quality of the newly formed bone tissue after eight months of the postoperative between the synthetic graft in a personalized block with the autogenous bone graft.

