**Methods:**

This is a split-mouth randomized clinical study designed to evaluate the performance of personalized (patient-specific) bioceramic bone grafts (Plenum^®^ Oss 3D_β_ fit) for bone augmentation of the atrophic anterior maxilla in comparison to the autogenous bone graft. We hypothesize that the gain and maintenance of the grafted area volume and the quality of the newly formed bone tissue after eight months postoperative with the synthetic patient-specific graft will be superior to the autogenous bone graft. To assess the quantity and the quality of bone neoformation, volumetric and histological analyses will be performed.

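### The primary endpoint is graft volume alone in the objectives and sample size, but volume plus an undefined bone quality in the hypothesis and endpoint list

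*Protocol article*

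**What the plan says.** The protocol article describes the primary endpoint in several places.

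- **Objectives {7}:** "The primary objective of this clinical investigation is to evaluate the increase/maintenance of bone graft volume after eight months postoperative". The next sentence places tissue characterisation lower: "The secondary objectives include the analysis and characterization of the new bone formation according to the graft used".
- **Abstract, Methods:** the superiority hypothesis covers both: "We hypothesize that the gain and maintenance of the grafted area volume and the quality of the newly formed bone tissue".
- **Outcomes {12}, Primary endpoints:** here too there are two components, in these words: "Evaluate the gain of increase/maintenance of the volume of the bone graft area and the quality of the newly formed bone tissue". Which measurement stands for quality is not stated.
- **Outcomes {12}, Secondary endpoints:** the tissue measures appear here. They are the histological percentages, osteocalcin, BMP-2, alkaline phosphatase, VEGF and micro-CT mineralised volume.
- **Volumetric analysis:** resorption is the change between the post-graft scan and the scan eight months later.
- **Sample size {14}:** "the minimum difference between the means of treatments concerning the percentage of volumetric reduction of the graft was 11.90, with a standard deviation of 12.09". No quality measure enters the calculation.
- **Statistical methods {20a}:** one set of tests serves the data in general. No primary variable, division of alpha or success rule is stated.
- **Missing data {20c}:** participants are replaced until 20 have had a biopsy, and the reason given is the analysis of the primary endpoint.

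**The concern.** Quality of new bone is primary in two places and secondary in two others. The place that makes it an endpoint does not say what it is. Someone analysing the trial from this text cannot tell whether the superiority claim rests on volume, on quality, on either or on both.

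The replacement rule in {20c} suggests that quality is more than loose wording. Graft volume is read from CBCT and needs no biopsy, so a primary endpoint that is complete only at 20 biopsies implies a tissue outcome.

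The trial's main conclusion is at stake. The trial is open. If the quality variable is chosen after data are seen, an unpowered and previously unnamed measure could support the claim of superiority over autograft.

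**Working it through.** **Inputs.** From Sample size {14}: difference 11.90, SD 12.09, power 0.8, alpha 0.05, 20 participants with one graft of each type. Sidedness is not stated; two-sided is assumed.

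**1. The plan's own figure, for volume alone.**
- Standardised difference: d = 11.90 / 12.09 = 0.984.
- Normal approximation, per treatment: n = 2(1.960 + 0.842)² / 0.984² ≈ 16.2, so 17.
- Two-sample t-test: 17.2, so 18.
- Paired t-test, taking 12.09 as the per-side SD with zero correlation: 18.2, so 19. Taking 12.09 as the SD of the differences: 10.2, so 11.

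The two-sample t figure of 18 is within two of the stated 20, and 20 suffices on every one of these readings. The sample size is therefore consistent with one volume endpoint tested at 0.05.

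**2. Power for volume at 20 per treatment.** Noncentrality is 0.984 × √(20/2) = 3.11. The two-sided unpaired t-test gives 85.8% (87.5% by the normal approximation).

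**3. Two components, either sufficient, each at 0.05.**
- Independent: 1 − 0.95² = 9.75%.
- Upper bound whatever the correlation: 0.05 + 0.05 = 10%. Lower end, under complete dependence: 5%.
- With a Bonferroni split (0.025 each), volume needs 20.9, so 21 per treatment by t-test. Power for volume at 20 falls to 77.9%.

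**4. Two components, both required.** Alpha does not inflate, but joint power depends on the quality effect, which the protocol does not give.
- At 80% each and independent: 0.8² = 64%. The possible range over all dependence is 0.8 + 0.8 − 1 = 60% up to 80%.
- At 20 participants, if quality had the same standardised effect and were independent: 0.858² ≈ 74%.
- For 80% joint power under independence, quality alone would need 0.80 / 0.858 ≈ 93% power.

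**5. Where each section stands.**

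| Section | Volume | Quality of new bone |
|---|---|---|
| Abstract, Methods (hypothesis) | in the superiority claim | in the superiority claim |
| Objectives {7} | primary | secondary |
| Primary endpoints {12} | primary | primary, no variable |
| Secondary endpoints {12} | not listed | tissue measures listed |
| Sample size {14} | powered | absent |
| Missing data {20c} | not mentioned | implied by the biopsy criterion |

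**The case against.** The strongest reply is that the Objectives, Volumetric analysis and Sample size sections converge on volume, so the intended primary variable is clear and the rest is loose wording. That is a fair account of the likely intent, and it is why the repair is cheap. It does not remove the contradiction. The endpoint list and the hypothesis are the places a reader consults for the primary claim, and {20c} carries the tissue component into trial conduct. An analysis plan not shown here could add a multiplicity rule, but it would still have to depart from either the objectives or the endpoint list.

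A second reply is that the hypothesis and the endpoint join volume and quality with a conjunction, which reads at least as naturally as both being required. That stands. Alpha inflation is then only one of two possibilities and cannot be stated as fact.

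A reader might go further and infer that superiority could be claimed from any of nine tests: volume plus eight tissue measures. With independence that would give 1 − 0.95⁹ = 37%. The document does not support this. It lists those eight measures as secondary and never calls them the quality variables. Some, such as soft tissue and residual graft, do not describe new bone. They also come from the same biopsies, so independence is not credible. The text supports two primary components.

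**Conclusion.** The protocol contradicts itself on whether bone quality is primary, and where it is primary it has no variable and no success rule. This follows from the current text and needs no numerical assumption.

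The size depends on a rule that the document does not give. An either-suffices rule puts the false-positive rate at up to about 10%. A both-required rule leaves alpha at 0.05, but the power of 0.8 then describes volume only. The joint figures of 64% and about 74% are illustrations. They rest on independence and, respectively, on 80% power for each component or on quality having the same standardised effect as volume.

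The sample size itself is not at fault: 20 participants are adequate for volume as the single primary endpoint, on the protocol's own inputs and a two-sided test.

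**What to change.** Three edits are needed.

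1. In the abstract hypothesis and under Primary endpoints {12}, name one primary endpoint: the percentage reduction in CBCT graft volume from the 1-week to the 8-month scan, compared between grafts at 0.05, with sidedness stated. Define it by elapsed time, because T2 and T3 mean different visits in the Tomography section and the Participant timeline. This is the quantity in Volumetric analysis and Sample size {14}. It also fits the primary objective, whose looser wording can stay or be aligned.
2. Make quality of the newly formed bone secondary, as Objectives {7} already does.
3. In {20c}, make completion of the primary endpoint depend on the 8-month CBCT instead of the biopsy. Biopsies are still collected for the secondary endpoints.

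The cost is wording, plus a check that the registry entry agrees. The number of participants is unchanged. Quality results could no longer carry the superiority claim, which is a small loss because they were never powered. No fixed order among the secondary endpoints is required, and the implant stability and operative time comparisons stay as planned.

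If the sponsor wants quality to remain primary, the protocol must define its variable, say whether one or both components must succeed, state how alpha is allocated, and recalculate the sample size.

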#### Secondary endpoints

The secondary endpoints are as follows:Assess bone neoformation in the anterior region of the maxilla when the personalized block graft is used compared to the use of autogenous bone block graft. This will be done by evaluating the percentage of new-formed bone tissue, soft tissue, and the rate of residual material from the bone graftInvestigate whether the choice of bone graft interferes with the primary and secondary stability of implants installed in the region. Measures will be performed with RFA immediately after de implant placement and after 6 monthsEvaluate the influence of the graft on the maturation of newly formed bone tissue through the quantification of osteocalcin (OCN) from the biopsies retrieved just before the implant placementAssess the influence of the use of the graft type on the activity of osteoblastic cell differentiation through the quantification of morphogenetic protein-2 (BMP-2) from biopsies samplesEvaluate the influence of autogenous and personalized graft on collagen matrix production through alkaline phosphatase quantificationInvestigate the influence of the graft in the differentiation of endothelial cells through the quantification of vascular endothelial growth factor (VEGF)Evaluate the volume of mineralized new-formed bone tissue through micro-tomographic examinationsVerify the adaptation of the bone graft to the host boneEvaluate whether there is a difference in the operative time for performing the ceramic bone graft compared to the autogenous graft

